### Sample size

At least *N* = 73 participants were planned to be included. Using the approximation proposed by Twisk (25), and assuming an average correlation of 0.5 between measurements [as in (26)], this suffices, given the seven repeated measurements, to reach 80% power to detect a medium effect size of *d* = 0.5 between the treatment conditions. Using the more sophisticated power analysis approach proposed by Moerbeek et al. [(27), p. 191] for multilevel tests of a difference in linear slopes assessed with multiple (i.e., 7) measurements, for a medium effect size (*d* = 0.5) tested at a two-tailed significance level of 0.05, *N* = 39 suffices to reach 80% power. Starting with *N* = 73 and taking into account an early study dropout of 10%, the resulting N=66 suffices to reach > 95% power to detect a medium effect size (*d* = 0.5) and 80% power to detect a small-to-medium effect size of *d* = 0.38. An effect size of *d* = 0.5 between slopes is equivalent to a mean difference between conditions of approximately five points on the BPDSI at the last assessment, which is a relevant difference. Moreover, the sample size of N = 73 suffices to reach more than 80% power to detect at a significance level of 0.05, a difference of 30% in dropout rates during the first year between 20% [which is the approximate dropout rate of ST in individual-group format at 1 year; (26)] and 50%, which would be a substantial and alarming increase in the experimental treatment (25, 28).

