The following limitations of this study should be noted. First, in this RCT, early trauma treatment in ST is not compared to early trauma treatment in other evidence-based therapies for BPD, such as MBT, DBT, and TFP, nor is there a waitlist control group. When patients improve in both treatment arms and no differences between arms are found, it cannot be ruled out that non-treatment-specific factors (e.g., time and positive effects due to attention) can explain the improvement. This RCT has two arms, because a third treatment arm would make the execution of the trial much more complex because of the necessity of the availability of a third (evidence-based) treatment at each site, and a much higher N would be needed. In the current trial, ST-as-Usual is the control condition and the primary research question focuses on comparing the differences between the two ST conditions. Second, the study was powered only to detect medium effect sizes. Small effects of early trauma treatment on BPD severity and/or comorbidities and associated symptoms of BPD may not be detected. Third, the results cannot be generalized to treatments other than ST and ImRs. Fourth, the analyses that we will perform do not control for the total amount of ImRs that has been applied. This study will only investigate the effect of early application of ImRs vs. the current standard ST protocol, which does not prescribe the number of times ImRs is applied. With a positive effect of early ImRs, an interesting question for follow-up studies would be what the effects are of early ImRs, when the number of ImRs sessions is the same in both conditions.

In conclusion, this study is the first to compare the effectiveness of early trauma treatment in ST with regard to the course of BPD, treatment dropout, working alliance, and other secondary variables. Given the high prevalence of adverse childhood experiences in BPD, such insights are needed to further improve therapies for BPD. Additionally, the underlying mechanisms and predictors of (differential) treatment outcomes will be investigated, providing more insight into how treatments work and for whom treatments work. Therefore, this study will significantly extend our knowledge of trauma treatment for BPD.

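### The printed slope-test power (39 patients for 80%; 66 for over 95%) does not follow from half an SD at the last assessment with correlation 0.5, which gives about 70% at 66, and the inputs that would reproduce it are not stated

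*Protocol article*

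**What the plan says.** The Sample size section of the protocol article gives two calculations for the primary outcome.

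- The first uses an approximation for repeated measurements, "assuming an average correlation of 0.5 between measurements". It finds that 73 patients give 80% power for d=0.5 with seven measurements.
- The second is "for multilevel tests of a difference in linear slopes assessed with multiple (i.e., 7) measurements", "tested at a two-tailed significance level of 0.05". For d=0.5 it states that N = "39 suffices to reach 80% power". After 10% early dropout (73 × 0.9 = 65.7, so 66) it states that "the resulting N=66 suffices to reach > 95% power to detect a medium effect size" of d=0.5, and "80% power to detect a small-to-medium effect size of" 0.38.

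The section then says that d=0.5 between slopes is "equivalent to a mean difference between conditions of approximately five points on the BPDSI at the last assessment". The visits are at months 0, 4, 8, 12, 18, 24 and 36 (Procedure and assessments, Table 1). The Time frame section puts the last assessment three years after the last patient's start, so it is month 36. The Statistical analysis section has fixed effects for time, arm and their interaction, and lists random slopes as an option. The Discussion says that "the study was powered only to detect medium effect sizes".

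For the slope test the article prints no SD, residual variance, slope variance, covariance structure or time scale for d.

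**The concern.** The only time anchor given for d is the last assessment, and the only correlation given is 0.5. With these, a slope test needs roughly twice the 39 patients stated, and 66 patients fall well short of 95% power. What is at stake is how a null result would be read. With over 95% power claimed for a medium effect, readers would take half an SD at the last assessment as effectively excluded. If the true power for that effect is about 70%, they should not.

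**Working it through.** **Inputs.** Two-sided 5%, seven measurements, d=0.5, 66 patients after dropout (Sample size); 1:1 allocation (Randomization); visit months as above; correlation ρ=0.5 (first calculation only). Assumed, because not stated: d in total SDs, compound symmetry, no random slope, no clustering by therapy group, normal approximation.

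**Formula.** Let S be the sum of squared deviations of the visit times, divided by the square of the time at which d is reached. Then

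- N for 80% power = 4 × 7.849 × (1−ρ) / (S × d²), where 7.849 = (1.960 + 0.842)²
- power at N = Φ( d × √(N × S / (4(1−ρ))) − 1.960 )

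**1. First calculation.** N = 4 × 7.849 × (1 + 6 × 0.5) / (7 × 0.25) = 71.8, and power at 73 is 80.7%. The article's 73 reproduces.

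**2. Do the three slope figures agree with each other?** Yes. If 39 gives 80%, power at 66 is Φ(2.802 × √(66/39) − 1.960) = 95.4%, and the detectable d is 0.5 × √(39/66) = 0.384.

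**3. Literal reading: d reached at the last assessment, ρ=0.5.**

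- Equal spacing: S = 28/36 = 0.778. N = 15.698 / (0.778 × 0.25) = 80.7, so 81.
- Actual visits: the sum of squares is 2420 − 102²/7 = 933.7, so S = 933.7/1296 = 0.720. N = 15.698 / (0.720 × 0.25) = 87.2, so 88.

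| At N=66 | Equal spacing | Actual visits | Article |
|---|---|---|---|
| Power, d=0.5 | 71.7% | 68.4% | >95% |
| Power, d=0.38 | 48.6% | 45.7% | 80% |
| d with 80% power | 0.553 | 0.575 | 0.38 |

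A t reference distribution lowers the first row to 70.4% and 67.1%.

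**4. Random slopes.** A slope variance τ² (squared total SDs over 36 months) replaces (1−ρ)/S by (1−ρ)/S + τ². Taking SD 10 and actual visits, a slope SD of 3 points over 36 months (τ²=0.09) gives 63% at N=66, and 5 points (τ²=0.25) gives 55%.

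**5. Readings that recover the printed figures.**

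- *d reached at month 24, all seven visits, ρ=0.5.* S = 933.7/576 = 1.621; N = 15.698 / (1.621 × 0.25) = 38.7, so 39. At N=66, power is 95.5% for d=0.5 and 79.4% for d=0.38; the detectable d is 0.383. On a linear slope, 0.5 SD at month 24 is 0.5 × 36/24 = 0.75 SD at month 36, so five points there implies an SD of 5/0.75 = 6.7.
- *d reached at the last assessment with a higher correlation.* Setting N=39 gives 1−ρ = 39 × 0.25 × S / 31.396, so ρ = 0.758 (equal) or 0.776 (actual). At ρ=0.76 the first calculation becomes 31.396 × (1 + 6 × 0.76) / 1.75 = 99.7, about 100 patients instead of 73.

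**6. Other readings tried with ρ=0.5 that do not reach 39.** Arms constrained equal at baseline: 63 to 73. One-sided test: 64 to 69. Both together, equal spacing: 50. AR(1) with mean correlation 0.5: 207 to 213. d in residual SDs, equal spacing: about 161. d in slope SDs: at least 126. Only the six visits to month 24, with d reached there: 91.

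**The case against.** The strongest defence is that about 70% also depends on assumptions. The article prints 0.5 only for the first calculation, gives no standardiser for d, and cites a method whose inputs a condensed article may leave out. With the plan's own visits and correlation 0.5, anchoring d at month 24, when individual treatment has ended, returns all three printed figures. With no SD stated, five points at month 36 does not rule that out.

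This stands as far as it goes: the figures may have been computed correctly on unstated inputs. Several stronger inferences therefore fail.

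- A reader might infer that 39 needs a correlation of 0.76 to 0.78. The month-24 anchor shows that it does not.
- A reader might infer that 39 was a per-arm number mistaken for a total. Nothing in the text supports this, and the three figures agree as totals.
- A reader might infer that 39 beside 73 is contradictory on its face. A slope test and an average-difference test respond in opposite directions to the correlation, so it is not.
- A reader might fault the first calculation for losing power at 66. The article claims 80% by that method at 73 only, and that reproduces.

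The defence does not clear the paragraph. The text names the last assessment and nowhere ties d to month 24. On the month-24 reading, the effect called medium is 0.75 SD at the assessment named, and 0.383 becomes 0.383 × 1.5 = 0.575 SD there, the same detectable effect as in step 3. The higher-correlation reading conflicts with the printed 0.5 and undoes the 73.

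**Conclusion.** The point holds in this form: the slope-power figures do not follow from an effect of half an SD at the last assessment with the only correlation printed. On that reading 66 patients give about 68 to 72% power for d=0.5, and 80% power only for d of about 0.55 to 0.58. This assumes total-SD units, compound symmetry and no slope variance; random slopes lower it further. On the actual visits with correlation 0.5, the difference at month 36 detectable with 80% power is about 0.575 SD under either anchor, so the printed 0.38 cannot describe the last assessment unless the correlation is well above 0.5.

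A reader might go further and conclude that the trial is shown to have only 70% power, or that the authors miscalculated. The documents do not support that, because the SD, variance components and time anchor used are not printed. Nor does this show that 73 is too few: that number is supported by the first calculation.

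**What to change.** Choose one of two changes to the Sample size section.

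1. Restate the slope power for half an SD at month 36 on the actual visits: about 68% at N=66 (72% if equal spacing is assumed), and 80% for d of about 0.55 to 0.58. Name the assumptions: correlation 0.5, compound symmetry, no slope variance.
2. Keep 39, over 95% and 0.38, but print the time anchor of d, the SD, the correlation and the slope variance that produce them. Reconcile that correlation with the 0.5 of the first calculation, and say what each effect is in SDs and BPDSI points at month 36.

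In either case, align the limitation in the Discussion, so that medium refers to an effect of stated size at a stated visit. The cost is a text change. Under the first option, or under the second if the month-24 anchor was used, the power claim for the last assessment becomes less favourable. No extra patients and no change to design or analysis are needed.

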### Recruitment

Patients from participating mental healthcare centers were asked to participate in the study. At all sites, Dutch-speaking participants were recruited; however, at the Amsterdam site, an additional cohort of English-speaking (non-Dutch) participants was recruited, resulting in one group of patients who received treatment in English. The same standardized measures were used for the Dutch and English patients. Patients with a primary diagnosis of BPD according to DSM-5 were asked to participate in the screening procedure (24). Patients were given both written and verbal information about the study, and after they provided informed consent, the screening process commenced. The sample included BPD patients with and without comorbid PTSD. Figure 1 illustrates the patient flow from recruitment onward; to achieve the intended sample sizes, site coordinators kept the central research team informed of the progress of participant recruitment and any issues that arose during the study.

**Figure 1 F1:**
[figure not shown]
Flowchart of the study design.

### Randomization

When participants were eligible for participation and completed baseline assessments, they were randomized to one of the two arms A (early ImRs) or B (STAU) in a 1:1 proportion by an independent researcher, after checking the inclusion and exclusion criteria, using block randomization with randomized block sizes blocks (sizes 4 and 6), stratified by the center (for the Amsterdam site stratified for language) (29, 30). The allocated treatment condition was disclosed to the patient by their therapist during the first treatment session.

### Procedure and assessments

Patients were recruited from participating mental healthcare centers. Patients with a primary diagnosis of BPD, classified using the Structured Clinical Interview for Personality Disorders (SCID-5-PD) (22) by trained clinicians, were asked to participate in the screening process of the study. A check was performed to determine eligibility. This check concerned examining whether participants met the inclusion and exclusion criteria, and their willingness and ability to participate in 2-year individual and group schema therapy.

After the first eligibility check but before randomization, the baseline measurements (see Measures Section) and a motivational/availability interview assessing the participants' motivation were performed by an independent research assistant. After 4, 8, 12, 18, 24, and 36 months, assessments by an independent trained local research assistant blinded to the treatment arm were performed (Table 1). Each assessment took approximately 2.5 h. The results of the assessments were shared with the patients and therapists so that they could be used as routine outcome measures to track and discuss treatment progress. Participants who drop out of treatment and or the study will be asked to continue the study assessments; however, if the participant decides to withdraw from the study, a minimized exit assessment is conducted—if the participant consents, in which the primary outcome measure is assessed. Patients will receive a monetary incentive of 25 euros after completion of all assessments. All group ST sessions are video-recorded, and individual ST sessions are audio-recorded. A random sample will be selected from each site. Independent raters will evaluate a random selection of these recordings to evaluate treatment adherence and competence of group ST with the Group Schema Therapy Treatment Integrity scale (31) and individual ST with Schema Therapist Competency Scale [STCS-I-1; (32)]. The recordings will be destroyed 5 years after the primary study results have been published. The results of the baseline assessments were provided to the therapists to formulate the ST case conceptualization.

**Table 1 T1:** Overview of measures and assessment times.

**Instrument**	**Baseline**	**After 3 sessions**	**4 months**	**8 months**	**12 months**	**18 months**	**24 months**	**36 months**
CTQ-SF	•							
BPDSI	•		•	•	•	•	•	•
WHODAS 2.0	•		•	•	•	•	•	•
WAI-SR		•	•	•	•	•	•	•
BSI	•		•	•	•	•	•	•
PCL-5	•		•	•	•	•	•	•
QoL	•		•	•	•	•	•	•
Happiness	•		•	•	•	•	•	•
SMI-2	•		•	•	•	•	•	•
YSQ-R	•		•	•	•	•	•	•

### Ethical aspects

Patients received verbal and written information about the study, and they were asked to give their written consent after a clear explanation and time (minimum 2 days) for reflection on participation in the study. Participants are allowed to leave the study at any time, keeping their right to alternative treatment at the participating center. Therapists are allowed to withdraw a patient, in consultation with the participant, from treatment only in exceptional situations after consultation with the central investigators. The (research) data collected during this project will be stored and shared in a safe and secure manner using systems that are managed and maintained by the IT departments of the involved institutions and conform to privacy regulations. Due to the sensitivity of our (research) data, especially to protect the privacy of the research participants, as well as participants not having given consent to share their data with others, data on an individual level cannot be shared with others. The study protocol was approved by the local ethics committee of the Department of Psychology at the University of Amsterdam (2019-CP-10845).

### Treatment

ST, developed by Jeffrey Young, derives from cognitive behavioral therapy (CBT) (33). This approach integrates concepts from various theoretical frameworks such as attachment theory, psychodynamic therapy, and experiential therapies. Schema therapy employs extensive experiential techniques in conjunction with cognitive and behavior-focused methods. The therapeutic relationship is defined as “limited reparenting,” where the therapist, within the bounds of a professional therapeutic alliance, adopts a nurturing role akin to a 'supportive parent' for the patient and tries to fulfill the basic needs of the client. The underlying premise of schema therapy is that childhood trauma and unmet fundamental needs, compounded by biological and cultural factors, contribute to the development of early maladaptive schemas, fundamental mental frameworks encompassing self-perception, interpersonal dynamics, and one's outlook on the world. Additionally, the theory posits the existence of dysfunctional schema modes comprising emotional, cognitive, and behavioral states.

The treatment consists of a fixed combination of group sessions and individual sessions. Groups consist of a maximum of nine patients. ST starts with three individual pretreatment sessions over 4 weeks. The main treatment consists of a treatment phase and a maintenance phase. The treatment period lasts a maximum of 18 months and is divided into two phases. The active treatment phase lasts for 12 months and includes weekly group psychotherapy sessions of 90 min, as well as weekly individual psychotherapy sessions with a duration of 45–50 min. This is followed by 6 months of weekly group ST sessions and every 2 weeks individual ST sessions. After 18 months, participants end the group treatment. The maintenance phase lasts for 6 months and consists of biweekly individual ST sessions for the first 3 months, followed by one individual session per month for the next 3 months. In this study, the individual ST has two arms; both commence with 1 month of getting acquainted with the ST concepts, forming a working relationship, and formulating a case conceptualization. In months 2, 3, and 4, patients were allocated to one of two individual schema therapy conditions:

A. Early ImRs: ImRs of early childhood memories during 12 weeks.B. STAU: Schema therapy as usual. Experiential techniques are allowed but the use of ImRs is not allowed in the first 4 months.

One site delivers intensive day clinical treatment. The treatment duration at this site is 24 months, divided into four phases; phase 1 has a duration of 6 months in which group ST is given three times a week for 90 min plus one individual session with a duration of 45 min. In phase 2, months 7–12: group ST is delivered 2 times a week for 90 min, accompanied by one individual session every 2 weeks, for 45 min. In phase 3, months 13–18, GST is delivered once a week for 90 min, and individual sessions are delivered once every 2 weeks for 3 months and thereafter once a month. In phase 4, one group therapy session is provided every 2 weeks, and individual sessions once every 2 months.

Group ST follows the protocol of Farrell et al. (34) and individual ST the protocol of Arntz and van Genderen (9). Group and individual ST are coordinated during weekly peer supervision meetings. The groups are semi-closed: every 12 sessions, patients can be included until the group is complete, participants who complete 1.5 years of treatment leave the group, and in the following session, new patients enter the group.

#### Use of co-intervention

Patients are allowed to continue medication during the study. However, patients who began taking medication within 3 months before the initial screening were excluded from the study, or they could participate after 3 months. Except for crisis interventions, no other psychological or new pharmacological therapies are permitted during treatment. Medication use is closely monitored throughout the study period.

#### Escape medication/treatment

If the participants experience an acute crisis during the study, they are permitted to use other forms of therapy or medication. The use of such interventions or medication will not result in exclusion from the study but will be recorded, monitored, and reported.

#### Further treatment

After completion of the 1-year follow-up assessment, the therapists who performed individual ST meet the patient for an evaluation, using the outcomes of the assessments; at this point, it is determined whether additional treatment is necessary. The type, frequency, and intensity of the additional treatment are determined by the center's typical indication procedure. If patients request assistance during the 1-year follow-up period, an estimation is performed if the need for assistance outweighs the benefits of the intended 1-year treatment-free period.

#### Dropout, deviation from the treatment protocol, and follow-up

Patients are free to withdraw from the study at any point for any reason. In serious cases, such as when a patient severely disrupts the treatment process for other group members or frequently misses treatment sessions, therapists may remove patients from treatment after consultation with the researchers (pushout). Site coordinators are responsible for finding appropriate alternatives for patients who drop out or are pushed out of treatment. The reasons for the early termination of treatment will be monitored and recorded by the researchers. If patients make significant progress in treatment, therapists may deviate from the treatment length according to the ST protocols and end the treatment earlier or skip sessions. At the end of treatment, therapists advise patients not to start new treatment during the follow-up period and continue applying the techniques they have learned by themselves. Following completion of the follow-up assessment, the former therapist discusses the results with the patient and helps them determine whether additional therapy is necessary. If a patient requires further therapy, the therapist will assist them in identifying the type of therapy needed and provide a referral if the therapy is not available at the treatment site.

#### Therapists, training, and supervision

Therapists must meet the following criteria: (1) At least junior level training and registration according to the Dutch ST register; (2) (if group schema therapist) completed a recognized course in GST according to the Farrell and Shaw ST model (34); and (3) completed a 2-day ImRs training in which they learn the ImRs protocol as described in the study by Arntz and van Genderen (9) and Arntz (35). The therapists will meet each other for 1 h every week for peer supervision and may consult the study's ST supervisors (AK and AA) if necessary.

